### Objectives {7}

The broad objective of this study is to use an experimental design to test two smoke-free policy compliance support interventions: (A) a “compliance through reduction (via relocation and reduction in personal smoking) and cessation” intervention targets households with smokers and involves support to shift smoking practices to designated areas and reducing personal smoking, and deliver in-residence smoking cessation support services via trained peer educators and (B) a “compliance through resident endorsement” intervention involving voluntary adoption of smoke-free living environments through personal pledges, visible door markers and/or via social media. We will compare randomly sampled participants in buildings that receive A or B or A plus B to the NYCHA standard approach.

We seek to achieve the following specific aims:

Aim 1: Experimentally test if compliance support interventions reduce personal smoking behavior.

Aim 2: Experimentally test if compliance support interventions reduce secondhand smoke exposure.

Aim 3: Determine if the tobacco retail environment surrounding each building moderates the relationship between compliance support interventions and smoking-related outcomes.

We hypothesize that the reduction/cessation plus resident endorsement intervention will yield significantly larger reductions in personal smoking and second-hand smoke exposure, compared to standalone interventions and the standard approach.

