#### Sample Size {14}

Power analysis was conducted using software PASS.15 for the primary outcome (change in salivary cotinine over a year) in Aims 1 and 2. Sampling 16 clusters (buildings) with 4 subjects per cluster (smokers for Aim 1, non-smokers for Aim 2) in each arm, we have 128 subjects per group or 256 in groups with or without a specific type of treatment (e.g. resident endorsement vs. no endorsement, cessation vs. no cessation). We calculated effect size as group mean difference in unit of standard deviation (SD) of the outcome, based on a two-sided test for mean difference between two groups in a cluster-randomized design with power of 80%. To compare groups with and without specific type of treatment, the group size of 256 may detect effect size of 0.283SD, 0.299SD, 0.312SD at significance level alpha = 0.05 for intra-cluster correlation coefficient r = 0.1, 0.15, 0.2, respectively. To compare intervention arms to the control arm, we have 3 comparisons and use conservative Bonferroni adjustment for multiple tests on significance level that alpha = 0.0167 (= 0.05/3). The sample size of 128 subject per arm may detect effect size of 0.472SD, 0.499SD and 0.524SD for r = 0.1, 0.15 and 0.2, respectively, at alpha = 0.0167. To put these numbers in perspective, using mean and SD estimated from a study of smokers in Maryland, an effect size of 0.283SD would correspond to a mean difference in salivary cotinine between the two intervention groups of 55.3 ng/mL with group SD = 195.4 ng/mL for smokers and of 0.19 ng/mL with group SD = 0.672 ng/mL for non-smokers.124 For instance a mean difference in 5 cigarettes smoked per day in the same study was 59.6 ng/mL for smokers.124 In England, following the smoke-free legislation salivary cotinine declined from mean level of 0.36 to 0.07 ng/mL (mean difference 0.29 ng/mL) among non-smokers.125 These findings support that we have sufficient power to estimate the impact of our interventions. The study is powered on an 80% retention rate, which we have achieved in other studies. Reasons for attrition will be tracked; those lost to follow up will be compared to the final sample.

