## Statistical methods

### Statistical Methods For Primary And Secondary Outcomes {20a}

We will conduct intent-to-treat (ITT) and contamination-adjusted intent-to-treat (CA-ITT) analyses to estimate the effects of the smoking relocation/cessation and resident endorsement interventions compared to the standard program implemented by NYCHA (no treatment). CA-ITT analyses will account for unanticipated contamination between trial arms and be completed via two-stage instrumental variables regressions using the original random allocation codes per assigned unit. Preliminary data analysis will include examination of distribution and summary statistics of all variables by intervention groups at each time point. The continuous variables with skewed distribution will be properly transformed, if necessary, to reduce impact of extreme values or improve model fitting. We will use box-plots to examine how distribution of a quantitative variable varies by categories of a categorical variable, and use scatter plots and Spearman correlation coefficient to examine bivariate associations between quantitative variables. Chi-square and Kruskal-Wallis tests will be used to detect group differences in categorical and quantitative baseline variables, respectively. For successful randomization, we expect no difference in the distribution of all baseline variables among the four arms. The baseline variables that differ by intervention groups and are related to outcomes of interest will be controlled in the aim specific models.

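### The unrestricted claim of sufficient power rests on the pooled contrast at the lowest ICC; for each arm versus the standard approach, the same paragraph's figures give at most about 31–38% (smokers) and 61–71% (non-smokers) at its own benchmarks

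*Protocol article*

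**What the plan says.** Sample Size {14} bases power on one outcome: "for the primary outcome (change in salivary cotinine over a year) in Aims 1 and 2". The layout is "Sampling 16 clusters (buildings) with 4 subjects per cluster (smokers for Aim 1, non-smokers for Aim 2) in each arm", from which it concludes "we have 128 subjects per group or 256 in groups with or without a specific type of treatment". It then gives detectable effects at 80% power, two-sided, for two contrasts:

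- Pooled, with versus without a given treatment, alpha 0.05: 0.283, 0.299 and 0.312 SD at ICC 0.1, 0.15 and 0.2.
- Each arm versus control, alpha 0.0167 (Bonferroni for three comparisons): "The sample size of 128 subject per arm may detect effect size of 0.472SD, 0.499SD and 0.524SD for r = 0.1, 0.15 and 0.2".

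Only 0.283 SD is converted: 55.3 ng/mL for smokers (SD 195.4) and 0.19 ng/mL for non-smokers (SD 0.672). These are set beside 59.6 ng/mL, the difference that goes with 5 cigarettes per day, and 0.29 ng/mL, the fall among non-smokers after legislation in England. The conclusion follows: "These findings support that we have sufficient power to estimate the impact of our interventions".

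Objectives {7} states the comparison: "We will compare randomly sampled participants in buildings that receive A or B or A plus B to the NYCHA standard approach". Statistical Methods {20a} estimates effects "compared to the standard program implemented by NYCHA (no treatment"), and the model under Primary outcome takes the standard arm as its reference group.

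**The concern.** The closing sentence covers the interventions in general, but its support comes from one of six stated detectable effects, and the most favourable one. The three arm-versus-control effects stand in the same paragraph in SD units and are never put beside the benchmarks. When they are, every one fails to reach the benchmark.

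The introduction and abstract also describe the trial as adequately powered. If that is taken to cover arm versus standard, a null result for A, B or A+B could be read as evidence of no effect, although the contrast would probably miss a difference as large as the smoker benchmark.

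**Working it through.** **Inputs**, all from Sample Size {14} unless noted: SD 195.4 (smokers) and 0.672 ng/mL (non-smokers); benchmarks 59.6 and 0.29 ng/mL; alpha 0.0167 (arm) and 0.05 (pooled); ICC r = 0.1, 0.15, 0.2; 128 per arm and 256 per pooled side; 16 buildings × 4 subjects per arm per aim; 25% cotinine subsample, n = 128 in total (Outcomes {12}; Plans For Assessment {18a}).

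**Step 1. Reproduce the stated effects.** For K clusters of m subjects per side, SE = √[2(1 + (m − 1)r)/(Km)] in SD units, with a noncentral t on 2(K − 1) degrees of freedom.

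- Arm: 128 = 32 clusters of 4. At r = 0.1, SE = √(2 × 1.3/128) = 0.1425. The detectable effects are 0.472, 0.498 and 0.524 SD (stated: 0.472, 0.499, 0.524).
- Pooled: 256 = 64 clusters of 4. The normal approximation gives 0.282, 0.298 and 0.313 SD (stated: 0.283, 0.299, 0.312).

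The stated figures therefore follow from 32 and 64 clusters of 4, with no reduction for retention.

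**Step 2. Convert the stated effects to ng/mL.**

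| Contrast | ICC | SD units | Smokers (benchmark 59.6) | Non-smokers (benchmark 0.29) |
|---|---|---|---|---|
| Pooled | 0.10 | 0.283 | 55.3 | 0.190 |
| Pooled | 0.15 | 0.299 | 58.4 | 0.201 |
| Pooled | 0.20 | 0.312 | 61.0 | 0.210 |
| Arm vs standard | 0.10 | 0.472 | 92.2 | 0.317 |
| Arm vs standard | 0.15 | 0.499 | 97.5 | 0.335 |
| Arm vs standard | 0.20 | 0.524 | 102.4 | 0.352 |

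All six arm-level values exceed their benchmark. So does the pooled value for smokers at ICC 0.2.

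**Step 3. Power at the benchmarks on the stated counts.** The benchmarks are 59.6/195.4 = 0.305 SD and 0.29/0.672 = 0.432 SD. Working back from the stated effect, power = Φ[δ(2.393 + 0.842)/MDE − 2.393] for the arm contrast. Example for smokers at r = 0.1: 0.305 × 3.235/0.472 = 2.090; 2.090 − 2.393 = −0.303; Φ = 38%.

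- Arm vs standard, ICC 0.1/0.15/0.2: smokers 38/34/31%, non-smokers 71/66/61%. The noncentral t agrees.
- Pooled (noncentral t): smokers 85/81/77%, non-smokers 97–99%.

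**Step 4. Power on the section's own layout.** 16 buildings × 4 subjects = 64 per arm per aim, and 32 × 4 = 128 per pooled side. The figure of 128 per arm in Trial design {8} counts smokers and non-smokers together. Noncentral t, ICC 0.1/0.15/0.2:

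| Contrast | Detectable effect (SD) | Power, smokers | Power, non-smokers |
|---|---|---|---|
| Arm (16 × 4) | 0.685/0.724/0.760 | 17/15/14% | 36/32/29% |
| Pooled (32 × 4) | 0.406/0.428/0.450 | 56/51/48% | 85/81/77% |

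In ng/mL the arm-level effects are about 134–149 and 0.46–0.51, and the pooled effects about 79–88 and 0.27–0.30.

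**Step 5. Further losses, for scale.** With 80% retention (3.2 per building), arm-level power is 12–14% and 26–31%, and pooled power 43–49% and 72–79%. For cotinine, n = 128 is 32 per arm. The split by smoking status is not stated. Assuming 16 of each (range 8 to 24), ignoring clustering and using a normal approximation, arm-level power is about 6% (4–9%) for smokers and 12% (6–19%) for non-smokers. Pooled power is about 23% (14–32%) and 41% (23–56%).

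**The case against.** **The pooled contrast is planned.** This stands. Trial design {8} declares a factorial design, and the section on the primary outcome tests whether A and B act independently and, if so, moves to a model with an indicator for each. A comparison side that contains the other intervention is normal in such an analysis. A reader might infer that the paragraph translates the wrong contrast altogether; the documents do not support that. The fault is that one planned contrast carries a conclusion worded for all of them.

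**The benchmarks are not target effects.** This also stands. They are offered for perspective, and a reader who takes them as effects the plan calls realistic goes beyond the text. They are nevertheless the only support given for the sufficiency sentence, so they are a fair test of it.

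**The arm-level effects are disclosed.** They are, in SD units, and the SDs stand beside them. Disclosure does not rescue an unrestricted conclusion that those figures contradict.

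**The 31–38% and 61–71% describe no test the trial will run.** Largely right. The counts behind them do not match the layout, cotinine is taken from a quarter of participants, and the models are fitted to self-reported outcomes with cotinine as a check on reliability. The percentages show what the paragraph's own inputs imply. For that reason the ng/mL values in Step 2 should not simply be inserted in the protocol.

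**Conclusion.** The concern holds in this form: the sufficiency statement is supported only for the pooled contrast, and on the stated counts only at ICC 0.1 and 0.15 for smokers. For each arm versus the standard approach, the paragraph's own figures give about 31–38% power for smokers and 61–71% for non-smokers at its benchmarks. As far as the counts go, that is an upper bound. On 64 per arm per aim it is about 14–17% and 29–36%. The pooled contrast then reaches 80% for smokers at none of the three ICCs, and for non-smokers only at 0.1 and 0.15, before retention and subsampling.

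The figures assume, as the section does, that the quoted SDs apply to change in cotinine and that the ICC lies between 0.1 and 0.2. A smaller SD of change would raise the power. The conclusion concerns power for cotinine and does not show that the self-reported outcomes are underpowered.

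**What to change.** In Sample Size {14}:

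1. Recompute the detectable effects on the per-aim counts the design delivers (16 buildings × 4 subjects per arm, with the stated retention) and, for cotinine, on the 25% subsample.
2. Give the pooled and the arm-versus-standard effects in ng/mL at all three ICCs, beside the two benchmarks.
3. Replace the closing sentence with one that claims sufficiency only for the contrasts and ICCs where the recomputed figures support it.
4. State that the arm-versus-standard contrasts do not have 80% power at the benchmark effects and will be reported as estimates with confidence intervals.

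The cost is a recalculation, a rewritten paragraph and a less favourable stated power. Enrolment does not change.

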### Trial design {8}

The trial design is a borough-stratified, four-arm, factorial-design, cluster RCT that targets 64 randomly selected buildings (16 buildings per arm) in separate NYCHA developments. We are recruiting and following 8 randomly selected residents stratified by smoking status − 4 smokers and 4 non-smokers - per building (n = 512) into four arms: (1) reduction/cessation, (2) resident endorsement, (3) reduction/cessation plus resident endorsement and (4) the standard approach (128 participants per arm) as shown in Fig. 1. A partnering community-based organization, Health People, Inc., specializing in peer-to-peer health education will train and supervise peer educators (PEs) who will then deliver the designated interventions. Quantitative assessments via survey questionnaire, salivary cotinine measurements, as well as sensory building observations will be used to measure outcomes. We will be evaluating the efficacy of compliance support interventions in reducing personal smoking and exposure to second-hand smoke in public housing. In addition, we will also determine if the tobacco retail environment surrounding a given public housing building moderates the relationship between compliance support interventions and smoking-related outcomes.

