### Recruitment {15}

The primary method of recruitment will be via door knocking and lobby intercepts until we reach our targeted number of residents per group (4 smokers, 4 non-smokers in each building). We will make every attempt to retain participants and minimize attrition bias through a range of rapport building and retention techniques, incentives, and cultural adaptation of study materials. We have also powered the study based on 80% retention.

While the study presents minimal risks, participants may withdraw at any time upon request.

Alternatives available to participants outside the research context are simply not enrolling and attempting to serve the greater good by participating in other research or community service activities.

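### The protocol claims power at 80% retention, but its detectable effects assume that no participant is lost

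*Protocol article*

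**What the plan says.** The retention claim appears four times in the protocol article. Sample Size {14} states "The study is powered on an 80% retention rate, which we have achieved in other studies". Recruitment {15} states "We have also powered the study based on 80% retention", and the same sentence stands in Plans To Promote Participant Retention And Complete Follow-up {18b} and in the Discussion under loss to follow-up and attrition bias.

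The inputs to the power calculation, also in Sample Size {14}, are "Sampling 16 clusters (buildings) with 4 subjects per cluster (smokers for Aim 1, non-smokers for Aim 2) in each arm", from which the text concludes "we have 128 subjects per group or 256 in groups with or without a specific type of treatment". For arm against control at alpha 0.0167 the result is "The sample size of 128 subject per arm may detect effect size of 0.472SD, 0.499SD and 0.524SD" at intra-cluster correlations r of 0.1, 0.15 and 0.2. For the factorial comparison at alpha 0.05 it is 0.283, 0.299 and 0.312 SD.

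The enrolment numbers are in Trial design {8}: "4 smokers and 4 non-smokers - per building (n = 512) into four arms", with "4) the standard approach (128 participants per arm) as shown in Fig. 1". Recruitment {15} continues "until we reach our targeted number of residents per group (4 smokers, 4 non-smokers in each building") and mentions no over-recruitment.

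**The concern.** A statement that a study is powered on 80% retention means one of two things. Either the stated effects were computed on the numbers left after a 20% loss, or enrolment was inflated so that the planned numbers remain. Here the number enrolled and the number in the calculation are the same, so neither appears to have been done.

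The claim is the protocol's stated quantitative protection against attrition, and it would serve as the benchmark during follow-up. If it is wrong, retention of exactly 80% would be read as meeting the plan although the stated effects no longer have 80% power.

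**Working it through.** **Inputs.** From Sample Size {14}: two-sided test, 80% power, m = 4 per cluster, n = 128 per arm (alpha 0.05/3) or 256 per factorial group (alpha 0.05), r = 0.1, 0.15, 0.2. Retention is 80%, so m falls to 4 × 0.8 = 3.2, and n falls to 102.4 or 204.8.

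**Formula.** The standard error of the difference, in SD units, is √{2[1 + (m − 1)r]/n}. The detectable effect is the value at which the noncentral t test has 80% power. With k = n/m clusters per group, the degrees of freedom are 2k − 2 (cluster level) or 2n − 2 (subject level).

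**Step 1: reproduce the stated figures with no loss.**

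Arm against control, n = 128, m = 4, k = 32, df = 62. At r = 0.1 the standard error is √(2 × 1.3/128) = 0.1425. The stated 0.472 is 3.312 times this, which is the multiplier for 80% power at this alpha and df.

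| Comparison, no loss | r = 0.1 | r = 0.15 | r = 0.2 |
|---|---|---|---|
| Arm, stated | 0.472 | 0.499 | 0.524 |
| Arm, computed (df 2k − 2) | 0.472 | 0.499 | 0.524 |
| Factorial, stated | 0.283 | 0.299 | 0.312 |
| Factorial, computed (df 2n − 2) | 0.283 | 0.299 | 0.314 |
| Factorial, computed (df 2k − 2) | 0.285 | 0.300 | 0.316 |

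**Step 2: apply 80% retention to the same counts.**

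Arm against control at r = 0.1: the standard error is √(2 × 1.22/102.4) = 0.1544, and 0.1544 × 3.312 = 0.511.

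| Comparison, 80% retained | r = 0.1 | r = 0.15 | r = 0.2 |
|---|---|---|---|
| Arm, detectable effect (df 2k − 2) | 0.511 | 0.534 | 0.556 |
| Arm, power at stated effect | 72% | 74% | 74–75% |
| Factorial, detectable effect (df 2n − 2) | 0.307 | 0.320 | 0.333 |
| Factorial, detectable effect (df 2k − 2) | 0.308 | 0.322 | 0.335 |
| Factorial, power at stated effect (either df) | 73% | 74% | 74–75% |

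Rounding alpha to 0.0167 gives 0.555 in place of 0.556. The inflation does not depend on n: √{[(1 + 2.2r)/3.2] / [(1 + 3r)/4]} = 1.083, 1.071 and 1.061, which is 6–8%.

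**Step 3: a check that barely depends on n, alpha or df.** Within each set of stated effects, the squared ratio of the effect at r to the effect at 0.1 equals [1 + (m − 1)r]/[1 + 0.1(m − 1)]. Solving for m gives 4.08 and 4.03 for the arm-level set, and 4.03 and 3.75 for the factorial set. The figures were built on 4 per building, not 3.2.

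**Step 4: other readings of the claim.** With 6.4 retained of 8 residents in the buildings of the design (16 per arm, 32 per factorial group), the effects at r = 0.1 are 0.344–0.349 (factorial) and 0.561–0.589 SD (arm). If the 20% loss takes whole buildings from the 32 and 64 clusters of Step 1 and 4 per building remain, they are 0.316–0.319 and 0.515–0.531 SD. None of the 80%-retention versions tried yields both stated sets.

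**Step 5: the clusters one aim really has.** Combining m = 4 with n = 128 requires 32 buildings per arm; the design has 16. With 16 buildings of 4 (n = 64 per arm), the arm-level effect at r = 0.1 is 0.685 SD with no loss and 0.742 SD at 80% retention. Retention adds the same 8%.

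**The case against.** The strongest reply is that the retention point is secondary. The figures in Sample Size {14} imply twice the buildings that one aim has per arm, so the calculation must be redone anyway. On the true count the zero-loss effect at r = 0.1 is already 0.685 SD against the stated 0.472, a 45% increase, next to which 8% for attrition is small. The 0.511 SD above therefore describes no trial that will be run. This is correct as to size. It does not restore the allowance: correcting the count alone would leave a false retention statement in four sections.

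A second reply is that no single formula reproduces both sets of stated effects. The arm-level figures fit cluster-level degrees of freedom, while the factorial figures fit subject-level ones better and still differ by 0.002 at r = 0.2. That stands, and the factorial match is close rather than exact. But the mismatch is at most 0.004 SD, while 80% retention moves those figures by about 0.02 SD.

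A third reply is that the generalized estimating equations use all available data and that multiple imputation is planned, so a lost participant still contributes. This helps somewhat for outcomes with a 3-month assessment. It helps little for the outcome that the power analysis names, change in salivary cotinine, which is measured only at baseline and 12 months. The printed calculation credits no recovery from either method.

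The full protocol may hold more detail, but the finding is not that detail is absent. The article prints its inputs, its results and its claim, and the first two contradict the third.

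**Conclusion.** The concern holds. The stated detectable effects assume complete follow-up, so the 80% retention allowance does not exist. On the protocol's own counts, 80% retention raises the detectable effects by about 6–8% and lowers power at the stated effects to about 72–75% for arm against control and 73–75% for the factorial comparison.

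These figures assume that loss is spread evenly, leaving 3.2 per stratum per building, and that lost participants contribute nothing to the 12-month change. If whole buildings are lost instead, the arm-level effect on the stated counts at r = 0.1 is 0.531 SD rather than 0.511 SD (cluster-level df). The doubled cluster count and the collection of cotinine in only 25% of participants are separate matters; both make the position worse.

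**What to change.** Choose one of two changes.

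1. In Sample Size {14}, recompute the detectable effects on analysed numbers and state the inputs: 16 buildings per arm (32 per factorial group) and 4 × 0.8 = 3.2 analysed per stratum per building. With cluster-level degrees of freedom this gives 0.742, 0.775 and 0.806 SD for arm against control, and 0.439, 0.459 and 0.477 SD for the factorial comparison, at r = 0.1, 0.15 and 0.2. The building count must be corrected in the same step: applying 0.8 to the existing 128 and 256 would print 0.511 SD and still be wrong. These figures suppose that the outcome is measured in every participant. For cotinine, the analysed number must also reflect the 25% subsample.

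2. Delete the retention claim from Sample Size {14}, Recruitment {15}, the retention plans {18b} and the Discussion, and state that the detectable effects assume complete follow-up.

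The cost is one recalculation and wording in up to four sections. Enrolment need not change, and retention by itself makes the stated effects 6–8% less favourable. For comparison, keeping 128 and 256 completers at 80% retention would need 128/0.8 = 160 and 256/0.8 = 320 enrolled.
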